#### Kidney

In a systematic review by O’Callaghan et al. [29], delayed graft function was chosen as the main end point. For the largest trials assessing HTK solutions, the rates for this vary at around 30%. For Custodiol-N, an increase of this rate by one-half to 45% has been defined as noncritical. In order to reject the hypothesis that the delayed graft function rate increases by 15% or more at the alpha level of 0.025 with a power of 90%, 412 patients are needed. This sample size calculation is based on the score test of Farrington and Manning for a noninferiority test comparing two proportions. Autocorrelation effects caused by the transplant of two kidneys per donor to different patients have been assessed as negligible.

#### Liver

The success of liver transplantation is determined by the AUC of ALT measurements over the first 7 days after implantation. In a sample of 25 consecutively treated patients, the ALT level in the period between surgery and 5 days had an AUC of about 3800 mg*d/dl with a standard deviation of about 2000 mg*d/dL. Assuming a coefficient of variation of 0.5, in order to reject the hypothesis that the peak level rises by 25% or more at the alpha level of 0.025 with a power of 90%, 202 patients are needed. For sample size calculation, a two-sample *t* test of the mean ratio with lognormal data was used.

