#### Liver

After liver transplantation, the primary end point is the area under the curve (AUC) of alanine aminotransferase (ALT) during the first 7 days after surgery (minimum one measurement per day).

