#### Liver

The secondary end points after liver transplantation include the absolute peak serum lactate dehydrogenase (LDH) level within the first 7 days after transplantation, the peak serum ALT and LDH levels, and serum bilirubin, aspartate aminotransferase (AST), ALT, LDH, and total albumin levels, and prothrombin time at postoperative day 90. Further biliary complications (i.e. the number of episodes of cholestasis, therapy for cholangitis, episodes of biliary leakage and intrahepatic and/or extrahepatic biliary strictures) will be assessed.

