#### Follow-up

Follow-up will be performed daily up to day 7, and at postoperative days 30 (±3 days) and 90 (±7 days). These follow-up visits assess the recipient’s clinical status (ASA classification), biopsy-proven rejection episodes (according to Banff criteria), the recipient’s routine laboratory results (serum bilirubin, AST, ALT (a minimum of two times per day between days 1–7), LDH, total albumin) and prothrombin time after 30 days and 3 months, and biliary complications (number of episodes of cholestasis, therapy for cholangitis, episodes of biliary leakage and intrahepatic and/or extrahepatic biliary strictures). Additionally, the occurrence of any adverse advents will be recorded. Relevant concomitant medication (catecholamines, immunosuppression, anti-infectives, antihypertensives, antiarrhythmics, and diuretics) will be recorded in detail up to day 7 of follow-up and at days 30 and 90 after transplantation as ‘yes’ or ‘no’ only. Graft survival will be recorded, and parenteral nutrition will be checked.

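### The liver noninferiority null and its 25% margin are worded for peak ALT, but the primary end point is the 7-day ALT AUC, and the CV used for sizing comes from a 5-day AUC

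*Protocol article*

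**What the plan says.** All places are in the protocol article.

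- **Primary end points, Liver:** "the primary end point is the area under the curve (AUC) of alanine aminotransferase (ALT) during the first 7 days after surgery", with at least one measurement per day.
- **Secondary objectives, Liver:** the list includes "the peak serum ALT and LDH levels".
- **Sample size determination, Liver:** the paragraph opens with the primary variable: "The success of liver transplantation is determined by the AUC of ALT measurements over the first 7 days after implantation". It then gives the planning data: "In a sample of 25 consecutively treated patients, the ALT level in the period between surgery and 5 days had an AUC of about 3800", with a standard deviation of about 2000 in the same units. It assumes a CV of 0.5 and states the hypothesis: "in order to reject the hypothesis that the peak level rises by 25% or more at the alpha level of 0.025". With 90% power this leads to 202 patients, using a t test for a ratio of means with log-normal data.
- **Liver, Follow-up:** "ALT (a minimum of two times per day between days 1–7".
- **Analysis sets:** the liver and the kidney primary tests must both reject their nulls for a favourable result.

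**The concern.** One confirmatory test is described with three variables: the 7-day AUC as end point, the 5-day AUC as source of the variability, and the peak as subject of the null and margin. The liver sample-size paragraph is the only place in the article that states the liver null and the 25% margin. Because the liver test is one of the two that must succeed, its null is half of the success rule.

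A noninferiority margin has meaning only for the variable it was set for. Peak and AUC can move apart: a graft may reach the same peak and clear ALT more slowly, or the reverse. If the wording stays as it is, the quantity to which the 25% applies could be settled after results are known. A CV observed for a 5-day AUC also does not by itself establish the power for a 7-day AUC.

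**Working it through.** **1. Inputs.** From the liver sample-size paragraph: margin ratio 1.25, alpha 0.025, power 90%, assumed CV 0.5, planning mean about 3800 and SD about 2000, N = 202. From Randomization and blinding: 1:1 allocation, so 101 per arm. My assumptions: alpha is one-sided, because the hypothesis is noninferiority, and the true ratio is 1, because none is stated.

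**2. Reproducing the plan's figure.**
- Log-scale margin: ln(1.25) = 0.2231.
- Log-scale SD: σ = √ln(1 + CV²) = √ln(1.25) = 0.4724.
- Normal approximation per arm: 2(1.960 + 1.282)²σ²/0.2231² = 94.2, rounded up to 95, so N = 190. The exact noncentral t gives 96 per arm, N = 192.

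The stated 202 is about 5% higher. It is not reproduced by the stated method, but it errs on the safe side, and nothing below depends on the difference.

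**3. Power of 202 for a ratio margin of 1.25.** Noncentrality = 0.2231/(σ√(2/101)), with 200 df. At CV 0.5 it is 0.2231/(0.4724 × 0.1407) = 3.36, which gives 91.6%. The planning sample's own CV is 2000/3800 = 0.526.

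| CV of the analysed variable | σ | N for 90% | Power at N = 202 |
|---|---|---|---|
| 0.40 | 0.385 | 128 | 98.4% |
| 0.50 (assumed in plan) | 0.472 | 192 | 91.6% |
| 0.526 (planning sample) | 0.494 | 210 | 89.1% |
| 0.60 | 0.555 | 262 | 81.2% |
| 0.70 | 0.632 | 340 | 70.5% |

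Power at 202 is exactly 90% when the CV is 0.517. The article gives no CV for the 7-day AUC or for the peak, so it does not say which row applies. The rows other than 0.50 and 0.526 are what-ifs.

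**4. How far the 5-day window is from the 7-day window.** Assume, for illustration only, that ALT decays exponentially with a half-life h of 1 to 2 days. The share of the 7-day AUC that falls in days 5 to 7 is (2^(−5/h) − 2^(−7/h))/(1 − 2^(−7/h)).
- h = 1: 0.0234/0.9922 = 2.4%.
- h = 2: 0.0884/0.9116 = 9.7%.

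Under this model the two AUCs are close, and a large change in CV from the window alone is unlikely.

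**5. How far peak is from AUC.** In the same model the 7-day AUC is proportional to peak × h × (1 − 2^(−7/h)). With equal peaks and half-lives of 1 and 2 days, the AUC ratio is (2 × 0.9116)/(1 × 0.9922) = 1.84 while the peak ratio is 1.00. These are the ends of the assumed range, not a forecast. They show that a margin on one variable is not a margin on the other.

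**6. Sampling frequency.** The trapezoid AUC divided by the true AUC is (kD/2)coth(kD/2), with k = ln2/h and sampling interval D in days.
- h = 1: 1.0397 (D = 1) against 1.0100 (D = 0.5), a difference of about 3%.
- h = 2: 1.0100 against 1.0025, about 0.7%.

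**The case against.** The strongest reply is that the peak wording is a slip. The paragraph opens with the 7-day AUC, every planning figure in it is an AUC figure, the primary end point is defined plainly elsewhere, and Analysis sets ties success to the primary criteria. This largely stands. A reader might infer that liver success would be decided on a secondary end point; the document does not support that. What remains is that the article's only statement of the null and margin names a variable that is separately listed as secondary, and that sentence needs correcting.

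A second reply is that 202 patients are enough. This stands as far as it goes: the calculation depends only on the ratio and the CV, and 202 exceeds the 192 needed at CV 0.5. A reader might infer that the liver comparison is underpowered; the figures do not show that. Using 0.5 after quoting an approximate mean and SD is rounding, not an error, and costs less than one point against the stated 90%. The wide power range that follows from estimating a CV in 25 patients would exist with a perfectly matched end point, so it does not measure this defect.

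On sampling, "during the first 7 days after surgery (minimum one measurement per day" and the twice-daily minimum in Follow-up do differ. A reader might infer that patients sampled once daily would be dropped from the per-protocol set. That is speculation, because the list of excluding deviations is still to be drawn up. The 0.7% to 3% shift would bias the ratio in full only if one arm were sampled once daily and the other twice. The same mix in both arms largely cancels.

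Finally, this is a journal article. The full protocol and any SAP are not shown and may state the null correctly. The point concerns what the article states, not what it leaves out.

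**Conclusion.** The point holds as a misstated decision threshold. The liver null and the 25% margin are worded for the peak level, the primary end point is the 7-day ALT AUC, and the CV comes from a surgery-to-day-5 AUC. As written, no margin is stated for the primary end point, and the 90% power is not shown for it.

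It is not a demonstrated loss of power. If the 25% is meant for the AUC and the 7-day CV lies between 0.5 and 0.526, power at 202 is about 92% to 89%, assuming a true ratio of 1, log-normal data and one-sided 0.025. The window mismatch alone is probably small, but that rests on an assumed decay pattern. The difference between the sampling minimums is real and minor.

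**What to change.** - Before outcome data are seen, restate the liver null as: geometric mean ratio of ALT AUC over days 0 to 7 (Custodiol-N / Custodiol®) ≥ 1.25, if 25% on the AUC is the intended margin. If the 25% was chosen with the peak in mind, the margin for the AUC needs its own justification.
- Justify the CV for the 7-day window. Use the 25 planning patients if their day 6 and 7 values exist; the article documents only surgery to day 5. Otherwise state the CV as an assumption with a power range, as in the table above.
- Restate the power of 202 on that basis.
- Reconcile the two ALT sampling minimums, and compute the AUC from the same nominal times in every patient.

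The cost is a wording change and one recalculation, plus retrieval of later planning values if they exist. None of these steps in itself changes enrolment. The downside is that the stated liver power may become slightly less favourable.

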#### Combined kidney–pancreas

Very few pancreata are transplanted in Austria. We do not expect to collect enough data in a reasonable amount of time about the success rates of pancreatic transplantation. Therefore, data on success and safety will be collected on these patients but the results will only be presented in a descriptive way.

#### Analysis sets

All organs randomized and implanted or with an attempt to implant will be included in the analysis according to the randomized treatment group. Organs randomized but not implanted will count as screening failures.

All patients treated according to the study protocol will be included in the per-protocol set. A list of protocol deviations sufficient to exclude patients from this set will be compiled by the sponsor, the main investigator and the biostatistician before analysis starts. The primary analysis will be performed on the per-protocol set.

All tests of the primary criteria with respect to the liver and kidney would have to successfully reject the null hypothesis to support a favourable result with respect to Custodiol-N. Null hypothesis tests will be repeated for intention-to-treat sets.

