### Study medication

#### Treatment assignment

The reported organ donors are allocated according to the Eurotransplant guidelines without influence from the study. Only organs allocated to a patient who has signed the informed consent will be randomized.

Multiorgan donation is performed according to institutional guidelines. Organ perfusion is performed using Custodiol® as the standard preservation solution. Subsequently, organs allocated to a study centre with patients who have signed the informed consent will be randomized to either study medication. In case of simultaneous transplantation of the kidney and pancreas, both organs will be randomized together for the same study arm.

After randomization, back table perfusion with study medications will be performed via the renal artery for the kidney, the hepatic artery as well as the portal vein for the liver, and the mesenteric artery and portal vein for the pancreas using approximately 250–1000 ml of study medication per organ (Custodiol® or Custodiol-N). Subsequently, the grafts will be stored in 1000 ml of the study medication. The allocated study medication is provided to the recipient site. Before transplantation, back table perfusion using approximately 250–1000 ml of the study medication will be optionally performed.

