#### Randomization and blinding

Recipients with signed informed consent meeting all inclusion criteria and without any exclusion criteria will undergo transplantation with grafts that have been randomized to Custodiol® or Custodiol-N in a blinded manner. Grafts are randomized in a 1:1 ratio to receive either Custodiol® or Custodiol-N. After randomization, the randomized solution will be prepared for treatment at the donor site. Study medication will not be blinded for the investigator. Randomization will be performed using the web-based randomization service “Randomizer for Clinical Trials” developed at the Institute for Medical Informatics, Statistics and Documentation, Medical University of Graz, Austria.

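### Randomized grafts that are not implanted are labelled screening failures and, on the article's text, fall outside both analysis sets, although they may already have been exposed to the allocated solution

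*Protocol article*

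**What the plan says.** The protocol article, under Analysis sets, defines the analysed organs thus: "All organs randomized and implanted or with an attempt to implant will be included in the analysis according to the randomized treatment group". The next sentence is "Organs randomized but not implanted will count as screening failures". The per-protocol set is limited to patients treated according to the protocol, and "The primary analysis will be performed on the per-protocol set". The supportive analysis is given in one line, "Null hypothesis tests will be repeated for intention-to-treat sets", with no further definition of those sets.

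Treatment assignment gives the order of events. The donor is perfused with standard Custodiol in both arms, and the organ is then randomized. "After randomization, back table perfusion with study medications will be performed via the renal artery for the kidney", with corresponding routes for liver and pancreas. "Subsequently, the grafts will be stored in 1000 ml of the study medication". A further back-table flush before transplantation is optional.

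Randomization and blinding says "Study medication will not be blinded for the investigator". Packaging and labelling says that packages and bags openly carry the product name.

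Two other places bear on the point. Sample size runs recruitment until the target number of recipients has been enrolled, treated and followed up. Period of observation and documentation starts adverse event recording at transplantation.

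**The concern.** A screening failure normally occurs before randomization. Here the graft is the randomized unit, and between randomization and implantation it receives the intervention under test. If it is then declined because of its condition, the allocated solution may have contributed, and the allocation is not concealed from the investigator. Removing such a graft conditions the analysis on a post-randomization event.

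In a noninferiority trial the direction matters. If more poor grafts are removed from the Custodiol-N arm, the remaining grafts look better and the test moves towards success. The usual safeguard is to repeat the per-protocol analysis on the intention-to-treat set. On the article's text that does not help, because both sets start from implanted or attempted organs. A non-implanted graft also does not count towards the 412 or 202 and opens no adverse event record, so nothing else in the article would bring the loss to light.

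**Working it through.** **Which set could hold a non-implanted graft?**

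- Per-protocol set: patients treated according to the protocol. A graft never implanted has no treated patient, so it is out.
- Intention-to-treat set: the only description is organs implanted or with an attempt to implant. A graft with neither is out.
- An attempted but failed implantation is kept by the first sentence, yet can be read as not implanted under the second. The two sentences overlap.

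**Can exclusion follow exposure?** The order is randomization, flush with allocated solution, storage in it, optional second flush, implantation. Non-implantation at any point after the first flush is after exposure.

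**Inputs for a kidney illustration** (Sample size determination, Kidney): control delayed graft function (DGF) 30%, margin 15 points (45%), alpha 0.025 taken as one-sided, Farrington-Manning score test, 412 patients, hence 206 per arm at 1:1. Discard rates are not in the documents; those below are assumptions.

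**The plan's own figure.** With 30% in both arms and 90% power, the Farrington-Manning formula gives 195.2 per arm, or 392 in total, against the stated 412. Exact power at 206 per arm is 91.5%. The stated number is somewhat conservative, and this does not affect the present point.

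**Effect of discards at the margin.** Let a share d of an arm be discarded and a fraction q of those be grafts that would have failed. With true rate p, the rate among the remaining grafts is (p − d·q)/(1 − d). For example, with p = 0.45, d = 0.03, q = 1: (0.45 − 0.03)/0.97 = 0.433. The false noninferiority rate is the exact rejection probability of the score test at the two resulting rates, with 206 analysed per arm.

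| Discarded, Custodiol-N / Custodiol | q | Apparent rates | Difference | False noninferiority |
|---|---|---|---|---|
| 0% / 0% | – | 45.0% / 30.0% | 15.0 | 2.5% |
| 2% / 0% | 1 | 43.9% / 30.0% | 13.9 | 4.3% |
| 3% / 0% | 1 | 43.3% / 30.0% | 13.3 | 5.5% |
| 5% / 0% | 1 | 42.1% / 30.0% | 12.1 | 9.1% |
| 2% / 0% | 0.75 | 44.4% / 30.0% | 14.4 | 3.3% |
| 3% / 0% | 0.75 | 44.1% / 30.0% | 14.1 | 3.9% |
| 5% / 0% | 0.75 | 43.4% / 30.0% | 13.4 | 5.2% |
| 3% / 2% | 1 | 43.3% / 28.6% | 14.7 | 2.9% |
| 5% / 3% | 1 | 42.1% / 27.8% | 14.3 | 3.6% |
| 2% / 2% | 1 | 43.9% / 28.6% | 15.3 | 2.2% |
| 3% / 3% | 1 | 43.3% / 27.8% | 15.5 | 2.0% |
| 5% / 5% | 1 | 42.1% / 26.3% | 15.8 | 1.7% |
| any, unrelated to outcome (q equals the arm's own rate) | – | 45.0% / 30.0% | 15.0 | 2.5% |

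With equal discards and q = 1 the apparent difference is 0.15/(1 − d), which exceeds the margin, so the test becomes conservative.

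**Power if discards are kept and counted as failures.** With no true difference and equal discard d, the rate in each arm is 0.30(1 − d) + d. This gives 31.4%, 33.5% and 37.0% for d of 2%, 5% and 10%, and exact power at 206 per arm of 90.9%, 90.1% and 88.5%, against 91.5% with none.

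**The case against.** The strongest defence is that both primary endpoints need an implanted graft: dialysis in the first week after transplantation, and ALT over the first 7 days after surgery. A graft that is never implanted has neither, so an implanted-or-attempted set for the primary tests is defensible. The article also keeps attempted implantations in the randomized arm. This stands, and the fix leaves that set alone.

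A reader might infer that unblinded staff will discard Custodiol-N grafts and so bias both primary comparisons. The documents do not support that. They say the investigator is not blinded, but not who declines a graft, when, or on what grounds, and they give no rate. Both arms share the initial Custodiol perfusion, and only organs already allocated to a consenting recipient are randomized, so some quality rejection may come before randomization. Later non-implantation may have recipient or logistic causes.

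A reader might also infer that these grafts are certainly dropped from every set. That rests on the absence of a separate intention-to-treat definition, and the full protocol or analysis plan may supply one. Reporting of reasons by arm may sit there too, so its absence from an article is no fault in itself. What remains is the stated rule: a randomized, possibly exposed graft is classed as a screening failure.

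**Conclusion.** The point holds as a badly fixed rule with a conditional risk of bias. On the article's text, randomized grafts that are not implanted are in neither analysis set. Exclusion can follow exposure to an openly labelled allocated solution, and the intention-to-treat repeat would not reveal an imbalance.

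The size depends on two things that the documents do not give: how discards split between arms, and how strongly they relate to outcome. For the kidney, the range for 2% to 5% discarded runs from 1.7% (equal discards, all failures) to 9.1% (5% in the Custodiol-N arm only, all failures), against a nominal 2.5%. The figures of 4.3%, 5.5% and 9.1% are worst cases, not expectations. They also treat discard as equivalent to DGF, although the 15-point margin was set for DGF alone. No liver figure was computed, so nothing is claimed about the size of any effect on the ALT comparison. The remedy is a cheap improvement and does not require a redesign.

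**What to change.** 1. Keep the implanted-or-attempted set for the primary tests, and reword the two sentences so that an attempted but failed implantation clearly belongs to it.
2. Stop calling randomized grafts screening failures. State whether grafts declined after exposure belong to the intention-to-treat set.
3. Account for every randomized graft by arm, with the timing of non-implantation (before or after exposure) and the reason (graft quality, or recipient or logistic), the reasons being classified without knowledge of arm.
4. For kidney, add a sensitivity analysis that counts post-exposure graft-quality discards as DGF, labelled as a composite because the margin was set for DGF alone.
5. For liver, add a supportive rank-based analysis or a comparison of discard proportions by arm. A worst-rank score does not fit the lognormal mean-ratio *t* test on which the liver sample size is based, so it should not be inserted into that test.

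The cost is one eCRF field for reason and timing, one extra analysis, and a slight loss of power in the kidney sensitivity analysis if discards are equal in both arms (90.9%, 90.1% or 88.5% at 2%, 5% or 10%). The primary analysis and the sample size do not change.

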#### Packaging and labelling

Trial medication will be provided by the sponsor as 1-litre bags (3 litres for one patient) and the appropriate amount of lyophilisate per bag to the distributing pharmacy. Packages will be opaque and labelled with either “Custodiol®” or “Custodiol-N” in an unblinded fashion and with the study title, EudraCT number and “Zur klinischen Prüfung bestimmt”, according to the Directive 2001/20/EC of the European Parliament. Each bag will be labelled in the same way. To ensure allocation concealment, clinical monitors will check that unused medication packages have not been opened.

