#### Screening of the recipient

The screening visit includes a check of the inclusion and exclusion criteria (to test female patients ≤55 years for pregnancy), assessment of demographic data (age and gender) of the recipient, and informed consent by the study team. Within 24 h before transplantation, the recipients’ routine laboratory results (serum creatinine, creatinine MDRD clearance and urea) are recorded. Diuresis is also assessed. Additionally, the occurrence of adverse advents and concomitant medication will be recorded. Events compromising the blinding of the patient will be recorded as protocol deviations.

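### The plan does not say what follows if the per-protocol test succeeds and the intention-to-treat test fails, and it does not require exclusions to be defined blind to arm and outcome

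*Protocol article*

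**What the plan says.** All of the decision rules are in the Analysis sets section of the protocol article.

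- **Primary set:** "The primary analysis will be performed on the per-protocol set".
- **Success rule:** "All tests of the primary criteria with respect to the liver and kidney would have to successfully reject the null hypothesis". This sentence names no analysis set.
- **Intention-to-treat:** "Null hypothesis tests will be repeated for intention-to-treat sets". No consequence is attached to a failed repeat.
- **Exclusions:** the list of deviations that remove a patient from the per-protocol set "will be compiled by the sponsor, the main investigator and the biostatistician before analysis starts".
- **Organs not implanted:** "Organs randomized but not implanted will count as screening failures". The wider set is therefore organs randomized and implanted, or with implantation attempted, analysed as randomized.

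On blinding, the Randomization and blinding section says "Study medication will not be blinded for the investigator", and under Packaging and labelling the packs are "labelled with either “Custodiol®” or “Custodiol-N” in an unblinded fashion". The recipient screening sections mention blinding of the patient only: "Events compromising the blinding of the patient will be recorded as protocol deviations". The article does not say whether the sponsor or the biostatistician is blinded.

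**The concern.** Per-protocol exclusions happen after randomization. If they depend on arm and on outcome, the comparison is no longer protected by randomization, and a result close to the margin can cross it. The usual safeguards are to require that the intention-to-treat analysis agrees, and to settle the exclusions without sight of arm or outcome. The article states neither.

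Both primary outcomes are known by day 7: dialysis in the first week for kidney, and the ALT area under the curve over 7 days for liver. The trial is expected to run for about 48 months. The only stated deadline for the list would be met by a list written after every outcome is on record. The claim of noninferiority for the new solution is what is at stake.

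**Working it through.** **1. Inputs.** From the kidney sample-size section: control rate of delayed graft function 0.30, margin 0.15 (so 0.45 lies on the margin), one-sided alpha 0.025, power 90%, N = 412, Farrington-Manning score test. Allocation is 1:1, so 206 per arm. The article gives no exclusion rate or pattern, so every exclusion pattern below is an assumption.

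**2. The plan's own figure.** With 0.30 in both arms, the restricted estimates under the null are 0.3852 and 0.2352.
- s0 = sqrt(0.3852 × 0.6148 + 0.2352 × 0.7648) = 0.6456
- s1 = sqrt(2 × 0.30 × 0.70) = 0.6481
- n per arm = (1.960 × 0.6456 + 1.2816 × 0.6481)² / 0.15² = 195.2, so 196 per arm and 392 in total

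The stated 412 is somewhat larger and gives 91.5% power. The difference is conservative and does not bear on this point. It only confirms that the test is set up as the plan describes.

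**3. Can the two sets disagree after very few exclusions?** The statistic is z = (difference − 0.15) / SE, with SE from the restricted estimates, and it must be at or below −1.960. The event counts are assumed.

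| Set | Custodiol-N | Custodiol | Difference | SE | z | Result |
|---|---|---|---|---|---|---|
| All patients | 75/206 | 62/206 | 0.0631 | 0.0460 | −1.889 | fails |
| Two Custodiol-N events removed | 73/204 | 62/206 | 0.0569 | 0.0460 | −2.023 | passes |
| Two events removed from each arm | 73/204 | 60/204 | 0.0637 | 0.0460 | −1.876 | fails |

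Two one-sided exclusions, 1% of an arm (2/206), reverse the kidney result. The plan would then report a successful primary test and a failed repeat, and has no rule for that case.

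**4. False noninferiority rate at the margin (0.45 against 0.30).** Remove k Custodiol-N patients, all with the event. The rate in that arm becomes p = (206 × 0.45 − k) / (206 − k), and the rejection probability is Φ[(0.15 − (p − 0.30) − 1.960 × SE0) / SE1].
- k = 0: p = 0.450, argument −1.960, rate 2.5%
- k = 5 (2.4% of the arm): p = 87.7/201 = 0.4363; (0.0137 − 1.960 × 0.0473) / 0.0474 = −1.67, rate 4.8%
- k = 10 (4.9%): p = 82.7/196 = 0.4219; (0.0281 − 1.960 × 0.0474) / 0.0476 = −1.36, rate 8.6%

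Exact enumeration over both binomials, removing the events directly, gives 2.5%, 5.0% and 9.1%.

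**5. How far this depends on the pattern.**
- Same enumeration, with 5 events removed from each arm: 2.3%. With 10 from each arm: 2.2%. There is no inflation.
- A milder one-sided pattern, 5% of the Custodiol-N arm excluded with an 80% event risk among them: p = (0.45 − 0.05 × 0.8) / 0.95 = 0.4316, rate 5.8%.

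These rates are for the kidney test. A favourable overall result also needs the liver test to reject. No corresponding error rate was computed for liver.

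**6. Power.** With no exclusions the two sets coincide and power is unchanged: kidney 91.5% at 412, liver 91.6% at 202. If 5%, 10% or 20% are excluded without selection, per-protocol power is 90.0%, 88.4% or 84.4% for kidney and 90.0%, 88.3% or 84.4% for liver. That reduction is already built into the present plan, because the per-protocol set is primary. Requiring both sets adds only the loss from cases where the per-protocol test rejects and the intention-to-treat test does not.

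**The case against.** **Per-protocol is a recognised primary set for noninferiority.** This stands. Intention-to-treat can dilute a real difference, and the plan does repeat the tests in that set. It would be wrong to infer that choosing the per-protocol set is itself an error, or that intention-to-treat was ignored. What remains is that the repeat has no stated part in the decision.

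**The success sentence might cover the repeats.** It names no set, so the reading is possible. But the repeats are introduced only after it, and the primary analysis has just been tied to the per-protocol set. If agreement was meant, one sentence settles it.

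**A reader might infer that the list will be made late and by unblinded people.** The text does not support that. The deadline is an outer limit and allows a list made at any earlier time. Only the investigator is expressly unblinded; for the sponsor and the biostatistician the article is silent. It also describes compiling a list of deviation types, not choosing patients one by one with outcomes in view. The supportable statement is that the text permits knowledge of arm and outcome and states no safeguard against it.

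**The list and a blinded review may be in a separate analysis plan.** They may, and their absence from an article is no fault. The point rests on what the article fixes: the primary set, who compiles the list, and the deadline.

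**The inflation is a worst case.** Agreed. It comes entirely from one-sided exclusion of events. The article expects very few losses, and deviations in delivering the solution arise before the outcome.

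**Conclusion.** The point holds in limited form. Followed as written, the plan allows a noninferiority claim that the intention-to-treat set does not support, and it allows the exclusion list to be made with knowledge of arm and outcome. It does not show that either will happen.

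The size is an upper illustration and not a forecast: about 5% with 5 exclusions and about 9% with 10, against a nominal 2.5%. It rests on a true difference exactly at the margin and on exclusions confined to Custodiol-N patients with delayed graft function. Balanced exclusions leave the rate at or below nominal. This is a cheap improvement to the decision rule and not a defect that invalidates the design.

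**What to change.** 1. Keep the per-protocol analysis, and state that for each organ the null hypothesis must be rejected in both the per-protocol set and the intention-to-treat set, the latter as the article defines it (randomized and implanted, or implantation attempted). Each test stays at one-sided 0.025. No alpha split is needed, because requiring both to pass cannot raise the error rate above that of either one.
2. Fix the list of excluding deviations now, by amendment or in the analysis plan.
3. Classify patients against that list from listings that show neither arm, dialysis nor ALT, and record the classification before the data are unblinded for analysis.

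The cost is wording, the preparation of masked listings, and a small loss of power when the two sets differ. If nobody is excluded there is no loss.
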